#### 9.2.3 Safety analysis

- 1) Primary safety outcome: A detailed list of composite bleeding events will be provided.
- 2) Secondary safety outcomes: A statistical description of pre- and post-treatment laboratory safety measurements will be presented. Cross-tabulations of pre- and post-treatment laboratory safety indicators and ECG will be listed to assess their clinical significance in terms of normal/abnormal transitions.
- 3) Adverse events: A detailed list of adverse events/reactions will be provided, along with an assessment of their relationship to the test medication.

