## **1. Study objective**

To evaluate the efficacy and safety of Qing-Xin-Jie-Yu Granules (QXJYG) for intermediate coronary lesions (ICL) in patients with stable coronary artery disease (SCAD).

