## **5.3 Safety outcomes**

### 5.3.1 Primary safety outcome

- 1) the composite events of type 2, 3, or 5 bleeding as defined by the Bleeding Academic Research Consortium (BARC).

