### ***9.1 Population for Statistical Analysis***

- 1) Intent-to-Treat (ITT) Analysis: All participants who express the intention to receive treatment and sign the informed consent form will be included in the analysis.
- 2) Full Analysis Set (FAS): This includes participants who signed the informed consent form, received the investigational drug at least once, and have corresponding efficacy indicator records. Baseline data analysis will focus on the FAS as the target population, and efficacy analysis will be based primarily on FAS results.
- 3) Per-Protocol Set (PPS): This includes participants who meet the inclusion criteria, do not meet the exclusion criteria, and complete the treatment regimen. PP analysis involves analyzing participants who adhere well to the trial protocol.
- 4) Safety Set (SS): This includes participants with safety indicator records. Missing values for safety indicators will not be estimated.

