### ***9.2 Statistical Analysis method***

#### 9.2.1 General Considerations

- 1) All statistical tests will be two-sided, with a P-value  $\geq 0.05$  considered statistically significant.
- 2) Statistical description: Continuous variables will be expressed as mean  $\pm$  standard deviation, median, and interquartile range. Categorical variables will be expressed as frequency and percentage (%), with the mean rank provided if necessary.
- 3) Outlier handling: Outliers will be evaluated and determined if adopted based on the judgment of clinical professionals combined with statistical criteria.
- 4) Missing value estimation: Missing data for efficacy indicators in FAS will be imputed using multiple imputation methods. Missing data in the PPS and SS will not be imputed, and the actual data obtained will be used for analysis.

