  - Estimation: The least squares method will be used to estimate the mean difference between groups and the 95% CI.
- c) Serum inflammatory factors, blood lipids, and carotid ultrasound indicators
- Description: Values at baseline and 6 months after treatment, as well as the difference from baseline to 6-month will be described.
  - Intergroup Comparisons: A linear mixed model will be used, with the dependent variable being the difference from baseline to 6-month. Fixed effects include group and center, and random effects include the subjects, with baseline values as covariates.

- Estimation: The least squares method will be used to estimate the mean difference and 95% CI.
- 3) Endpoint Event: MACE
- Description: The incidence rate of MACE from baseline to the 1-year follow-up will be described.
  - Intergroup Comparisons: The Cox proportional hazards model will be used, with the dependent variable being the occurrence of MACE and the survival time variable being the time from baseline to either the occurrence of MACE or the end of follow-up. The primary independent variable is the group. Covariates include age, gender, BMI, systolic blood pressure, diastolic blood pressure, LDL-C, FBG, smoking status, alcohol consumption, family history of early-onset cardiovascular disease, presence of cerebrovascular disease, peripheral vascular disease, diabetes mellitus, hypertension, dyslipidemia, concomitant use of PCSK-9 inhibitors, and study center.
  - Estimation: The partial likelihood method will be used to estimate the hazard ratio and its 95% CI.
- 4) Subgroup analyses: Considering the significant impact of concomitant diabetes and the use of PCSK-9 inhibitors on drug efficacy, subgroup analysis of the primary efficacy outcome and endpoint events will be performed in SCAD patients with diabetes and SCAD patients with the use of PCSK-9.

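### Section 9.2.3 plans only a listing for the primary safety outcome (BARC 2, 3 or 5 bleeding) and for adverse events, with no between-arm estimate or confidence interval

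*Protocol*

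**What the plan says.** Section 1 gives the objective as "To evaluate the efficacy and safety of Qing-Xin-Jie-Yu Granules" in the target population. Section 5.3.1 makes the composite of BARC type 2, 3 or 5 bleeding the primary safety outcome. The flow chart in section 12 schedules its collection at months 2, 4 and 6, in both arms of a randomised, double-blind, placebo-controlled trial.

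Section 9.2.3 then sets out the safety analysis in three items:
- Primary safety outcome: "A detailed list of composite bleeding events will be provided".
- Laboratory measures: a statistical description, with normal/abnormal cross-tabulations that also cover the ECG.
- Adverse events: a detailed list, with an assessment of relationship to the test drug.

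Three other places bear on the point:
- Section 9.2.1 has a general rule: "Categorical variables will be expressed as frequency and percentage".
- Section 9.1 defines the Safety Set: "This includes participants with safety indicator records". It sets no dosing condition, whereas the Full Analysis Set requires at least one dose.
- Section 9.2.2 treats the other clinical event outcome, MACE, more fully: "The incidence rate of MACE from baseline to the 1-year follow-up will be described". It adds a Cox model giving a hazard ratio with 95% CI.

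**The concern.** The protocol is not silent on how the primary safety outcome will be analysed. It names a method, and that method is weaker than the one given to every efficacy outcome and to MACE. A list of events shows what happened to individual patients. It does not itself say how many patients in each arm had an event, how far the arms differ, or how large a difference the data leave open.

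What is at stake is interpretation. If few or no bleeds are listed, nothing written in the plan puts a bound on the excess that remains compatible with the data. With about 60 patients per arm that bound is wide, and a report should state it. The placebo arm exists to separate drug effects from background bleeding, and the safety section writes down no contrast with it.

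**Working it through.** **What is specified for each outcome**

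| Outcome | Description | Between-arm estimate | Interval |
|---|---|---|---|
| CT-FFR (9.2.2) | yes | mean difference | 95% CI |
| MACE (9.2.2) | incidence rate | hazard ratio | 95% CI |
| Laboratory safety measures (9.2.3) | statistical description, cross-tabulation | none | none |
| BARC 2, 3 or 5 bleeding (9.2.3) | list; percentage only through 9.2.1 | none | none |
| Adverse events (9.2.3) | list with causality; percentage only through 9.2.1 | none | none |

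Section 9.2.3 uses different terms for laboratory measures (a statistical description) and for bleeding and adverse events (a list). The natural reading is that the list means a listing.

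**What the missing interval would show**

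The protocol states no bleeding rate or safety precision, so there is no figure of its own to reproduce. Inputs: 120 patients (section 3.4), allocated 1:1 (section 3.2), so 60 per arm. All event counts below are assumptions.

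1. *No events in an arm.* Exact (Clopper-Pearson) 95% upper limit = 1 − 0.025^(1/60) = 0.0596, or 6.0%.

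2. *No events in either arm.* The Wilson upper limit for 0/60 is z²/(n + z²) = 3.8415/63.8415 = 0.0602. The Newcombe interval for the difference is 0 ± √(0² + 0.0602²), or about ±6.0 percentage points.

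3. *Some events.* With p the observed proportions, l and u their Wilson limits, and d = p1 − p2, the Newcombe limits are d − √[(p1 − l1)² + (u2 − p2)²] and d + √[(u1 − p1)² + (p2 − l2)²]. Take 6/60 against 3/60:
   - Wilson limits: 0.0466 to 0.2015, and 0.0171 to 0.1370.
   - Lower limit: 0.05 − √(0.0534² + 0.0870²) = −0.052.
   - Upper limit: 0.05 + √(0.1015² + 0.0329²) = 0.157.
   - Result: +5.0 points (95% CI −5.2 to +15.7).

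   For 3/60 against 1/60 the same method gives +3.3 points (−4.6 to +12.1).

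4. *Would a test help?* Exact power of a two-sided Fisher test at 0.05, 60 per arm, for a doubling of the control rate:

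| Assumed control rate | Power |
|---|---|
| 1% | 0.1% |
| 2% | 1.1% |
| 5% | 8.8% |
| 10% | 24.7% |

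A significance test would add little. The useful output is the estimate with its interval.

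**The denominator**

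Section 9.1 admits anyone with safety records to the Safety Set, and section 12 schedules laboratory tests and ECG at baseline. Taken alone, that wording would admit a never-dosed patient. Section 2.4, however, eliminates patients who took no study drug, by decision at blind review, but does not say from which analysis set. The same clause eliminates patients who used less than 10% of their drug. Section 2.5 lists adverse events as a reason for withdrawal, so this group could include people who stopped early because of one. If the clause applied to the Safety Set, it could remove dosed patients with events.

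**The case against.** The strongest reply has four parts.

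*The general rule supplies a rate.* Having a BARC 2, 3 or 5 event is a yes/no variable, so section 9.2.1 and the Safety Set together can produce a number and percentage per arm. This stands. A reader might infer that the trial will give no bleeding rate at all, and the protocol does not support that. What the rule does not supply is a difference, an interval, or a choice between counting patients and counting events.

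*A list does not exclude summaries, and details belong in the SAP.* Section 9.2.3 does not say that only a list will be given, and section 3.5.3 refers to a statistical analysis plan finalised before database lock, which is not at hand. It may add tables. But the protocol states an analysis for this outcome while specifying estimates and intervals for the others. A better method than the stated one is a fair point even if the exact CI formula is SAP material.

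*The placebo arm is used, and the objective can be addressed.* Bleeding is collected in both arms, nothing confines the list to one, and laboratory safety data are described. It would go too far to say that the placebo arm is ignored or that the listing prevents the trial from meeting its safety objective. The main limit on ruling out harm is the sample size, which was set for CT-FFR. The proposed table would report that limit without removing it.

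*Section 2.4 deals with never-dosed patients.* This stands in part. One cannot conclude that they will be in the Safety Set. Equally, the protocol does not say that section 2.4 governs that set, so its composition is unsettled.

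**Conclusion.** The point holds in this form: for the primary safety outcome and for adverse events, section 9.2.3 specifies a listing and no between-arm estimate or confidence interval, although safety is part of the objective and MACE receives both. A percentage per arm may follow from section 9.2.1; a difference with an interval does not.

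The size rests on 60 patients per arm and on assumed counts. With no events in either arm, the data would still be compatible with an excess of about 6 percentage points. With a handful of events, the interval would span roughly 17 to 21 points. An empty or short list is therefore not evidence that excess bleeding is absent. The Safety Set definition is a secondary weakness: it has no dosing condition, and its relation to section 2.4 is unstated.

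**What to change.** Amend section 9.2.3, and the Safety Set definition in section 9.1, before unblinding:

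1. For BARC 2, 3 or 5 bleeding to month 6, report by arm the number and percentage of patients with at least one event, with exact 95% CIs, and the risk difference with a Newcombe 95% CI. State that this is an estimate and not a powered test.
2. Report by arm the incidence of adverse events, adverse reactions and serious adverse events, counting patients.
3. Define the Safety Set as all patients who took at least one dose, analysed by treatment taken. State that the section 2.4 eliminations do not remove dosed patients from it.
4. Keep the listings as a supplement.

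The cost is one or two extra tables. All the data are already scheduled for collection, and neither the sample size nor the visit schedule changes.

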## ***2.5 Withdrawal criteria***

- 1) Conditions continue to worsen.
- 2) Comorbidities, complications, or special physiological changes.
- 3) Poor compliance or use of prohibited drugs.
- 4) Adverse events or serious adverse events.
- 5) Leak of blindness

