| CT-FFR                                 | X                     |                      |                      | X                    |                       |
| CCTA a                      | X                     |                      |                      | X                    |                       |
| SAQ                                    | X                     | X                    | X                    | X                    |                       |
| hs-CRP                                 | X                     |                      |                      | X                    |                       |
| MMP-9                                  | X                     |                      |                      | X                    |                       |
| Blood lipids a              | X                     |                      |                      | X                    |                       |
| Carotid artery ultrasound b | X                     |                      |                      | X                    |                       |
| Safety outcomes          |                       |                      |                      |                      |                       |
| Composite events of bleeding           |                       | X                    | X                    | X                    |                       |
| Laboratory test                        | X                     | X                    |                      | X                    |                       |
| Electrocardiogram                      | X                     | X                    |                      | X                    |                       |
| Adverse events                         |                       | X                    | X                    | X                    |                       |
| Endpoints                |                       |                      |                      |                      |                       |
| MACE                                   |                       | X                    | X                    | X                    | X                     |
| Medication adherence     |                       |                      |                      |                      |                       |

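### The normal/abnormal cross-table in section 9.2.3 cannot show worsening in patients already abnormal at baseline, and it does not say which post-treatment value it uses

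*Protocol*

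**What the plan says.** Section 9.2.3 of the protocol sets out three things that bear on laboratory and ECG safety.

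- For laboratory values: "A statistical description of pre- and post-treatment laboratory safety measurements will be presented".
- For laboratory values and ECG: "Cross-tabulations of pre- and post-treatment laboratory safety indicators and ECG will be listed", with clinical significance judged by movement between normal and abnormal.
- For adverse events: "A detailed list of adverse events/reactions will be provided, along with an assessment of their relationship to the test medication".

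The flow chart in section 12 schedules laboratory tests and ECG at baseline, month 2 and month 6. Section 9.2.3 does not tie post-treatment to any of these visits. It states no worst-value rule and no grading.

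On incomplete data, section 9.1 says of the Safety Set: "Missing values for safety indicators will not be estimated". Section 9.2.1 adds that this set is analysed on the data actually obtained. Section 2.5 lists "Adverse events or serious adverse events" among the grounds for withdrawal. Section 6 requires a safety evaluation when a patient discontinues.

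**The concern.** Section 5.3.2 makes coagulation, blood count, urine, stool, liver and renal function, blood glucose and ECG the secondary safety outcomes. The cross-table is where section 9.2.3 says their clinical significance will be assessed, so its scale decides which changes can be seen.

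Two features weaken it. The scale has two categories, so the size of a change is lost and a patient who begins abnormal cannot move further in the harmful direction. The pairing is one pre-treatment state with one post-treatment state, while two post-baseline measurements are scheduled and the text does not say which enters the table.

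At stake is a table that reports few or no harmful transitions when some patients have deteriorated. The primary efficacy analysis is not affected.

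**Working it through.** The protocol states no figure on this point, so there is none to reproduce. The check sets the sections side by side, with small counts to show scale.

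**Step 1. What a two-category table can register.** It has four cells: normal to normal, normal to abnormal, abnormal to normal, and abnormal to abnormal. Only normal to abnormal registers harm. A patient abnormal at baseline can fall only in the last two cells, which read as improvement or no change. This is true whichever visit supplies the post-treatment value.

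**Step 2. Whether such patients are in the trial.**
- Section 9.2.2 plans a subgroup with diabetes, so diabetic patients are admitted. Blood glucose and urine glucose are safety outcomes in section 5.3.2.
- Section 2.3, item 7, excludes cardiac, hepatic or renal insufficiency only when severe, and item 9 excludes hepatitis. Mildly raised ALT or creatinine at entry remains possible.
- All patients have coronary disease under section 2.2, so an abnormal baseline ECG is plausible. ECG is a safety outcome.

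**Step 3. Size of the blind spot.** Section 3.4 gives 120 patients in a 1:1 ratio, so 120 / 2 = 60 per arm. If a proportion b is abnormal at baseline on a test, 60 × b patients per arm cannot register harm on it. Each 10% gives 60 × 0.10 = 6 patients per arm. The documents do not give b for any test.

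**Step 4. Which post-treatment value is used.** Section 6 describes months 2, 4 and 6 alike as after treatment. Where section 9.2.2 wants only month 6, it says so, and for the SAQ it lists every visit. Section 9.2.3 does neither. Two readings follow.
- Both visits are tabulated: a month-2 abnormality that resolves is shown, and nothing is lost on this count.
- Month 6 only: it appears as normal to normal.

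**Step 5. Scale of the month-6-only reading.** Assume that a proportion p of 60 patients is newly abnormal at month 2 and a proportion r of those is normal again by month 6. Both are assumptions. The number abnormal at month 2 is 60p, and the number still visible at month 6 is 60p(1 − r).

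| p | abnormal at month 2 | visible at month 6, r = 50% | visible at month 6, r = 80% |
|---|---|---|---|
| 2% | 1.2 | 0.6 | 0.24 |
| 5% | 3.0 | 1.5 | 0.6 |
| 10% | 6.0 | 3.0 | 1.2 |

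On this reading, about 0.6 to 4.8 patients per arm would drop out of view (60p × r, from 1.2 × 0.5 to 6 × 0.8).

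**Step 6. Whether the other displays close the gap.**
- The statistical description names laboratory measurements, not ECG. Section 9.2.1 gives continuous variables as mean with standard deviation, median and interquartile range. These can leave a few outliers among 60 patients unseen.
- The adverse-event list shows an abnormality only if it was recorded as an event. Section 7 does not say when a laboratory result is one. The severity scale in section 7.2.1 rests on tolerability and need for treatment, so a symptomless enzyme rise may be rated mild or never listed.
- For ECG, the cross-table is the only dedicated display that section 9.2.3 names.

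**The case against.** The strongest reply is that the cross-table does not stand alone and that its detail belongs in the statistical analysis plan. Section 3.5.3 refers to such a plan, which was not available here. Choice of visit, worst-value rules and grade limits are commonly set there, and section 9.2.3 does not forbid them. Much of this stands, and it is why the point is minor. It does not remove the point, because the protocol itself fixes the criterion as transitions between normal and abnormal.

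A reader might infer four stronger things that the documents do not support.

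- **Patients withdrawn for toxicity vanish from the table.** Section 6 requires a safety evaluation at exit, and section 2.5.2 asks dropouts to complete as many assessments as they can. Declining to impute deletes nothing that was observed. A patient withdrawn for an adverse event also belongs on the adverse-event list. What remains is that section 9.2.3 does not say an exit value counts as post-treatment.
- **Month 2 is ignored by rule.** That is one reading of an undefined term, as step 4 shows.
- **The comparison between arms is biased.** Section 9.2.3 is descriptive and names no between-group test for these outcomes. The table may under-report harm; a bias of known direction and size cannot be derived.
- **The loss is large.** Take an assumed 5 of 60 patients with raised ALT at month 2 (8.3%), of whom two withdraw and two resolve. A month-6 table shows 1 of 58 (1.7%) only if both withdrawals also miss the required exit evaluation. With abnormal exit values counted it shows 3 of 60 (5.0%), and with month 2 tabulated all 5 of 60. The first figure is an assumed worst case, not an estimate.

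**Conclusion.** The point holds in a limited form, as a cheap improvement of minor severity.

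One part is certain and rests on no assumption about visits: a normal/abnormal table cannot show deterioration in patients who are abnormal at baseline. How many patients this concerns depends on baseline abnormality rates that the protocol does not give. It matters most for glucose in diabetic patients and for ECG.

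The second part is conditional: a month-2 abnormality that resolved is lost only if post-treatment means month 6. The counts for it rest on assumed rates.

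**What to change.** In section 9.2.3, make the following changes.

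- Present the tables by arm, with baseline against the worst value recorded after baseline. State that month 2, month 6, exit and unscheduled tests all count.
- Replace the two categories by prespecified graded classes for laboratory tests where a scale exists, for example multiples of the upper limit of normal or of the patient's own baseline. Include glucose.
- For ECG, add a worsened-from-baseline class.
- For tests that can be abnormal in either direction, such as white cells, state which direction is worst or tabulate both.
- Keep the planned normal/abnormal table as a second display and name the visit that it uses.

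The scheduled measurements are already in section 12, so no new visit or test is needed. The cost is extra tables. The downside is that worst-value tables show somewhat more isolated abnormalities in both arms, which is a reason to present the arms side by side.
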